#### Secondary outcome measures

Changes in sleep onset latency (SOL) will be measured by actigraphy [time frame: 28 days]. The investigators will measure patients’ sleep onset latency in minutes (time between registered bedtime in sleep diaries and first sleep onset measured by actigraphy) and compare the means of the difference for each participant between the two periods (A and B).Changes in number of awakenings measured by actigraphy [time frame: 4 weeks = 28 days]. The investigators will measure the number of awakenings between first sleep onset and the last wake up time registry and compare the means of the difference between periods (A and B) for each participant.Changes in wake after sleep onset (WASO) will be measured by actigraphy [time frame: 4 weeks = 28 days]. The investigators will measure patients’ total time awake between initial sleep onset and the final morning awakening (WASO) in minutes and compare the means of the difference between periods for each participant.Daily use of sedatives and hypnotics will be measured by medication registration use in sleep diaries [time frame: 4 weeks = 28 days]. The investigators will measure the change in total use of per need sedatives and hypnotics in mg by comparing the means of the difference for each participant between periods.Quality of sleep measured by questionnaire using the Pittsburgh Sleep Quality Index (PSQI) [time frame: data will be collected at baseline (visit 2), after 2 weeks (visit 3), and after 4 weeks (visit 4)]. The investigators will measure and report the change in quality of sleep between period A and B. For each participant, the difference between the PSQI measured at the first and the last visit (2 weeks apart) of the exposure period will be subtracted from the difference between the PSQI measured at the first and the last visit (2 weeks apart) of the control period. The total Pittsburgh Sleep Quality Index Score between 0 and 21, with “0” indicating no difficulty and “21” indicating severe difficulties, is reported. Because there will be less than 30 days between assessment at visit 3 and visit 4 and the standard PSQI is a retrospective 30-day instrument, we will use a modified version of the PSQI in which the patients will only be asked about their subjective sleep quality during the past 14 days.Symptoms of depression will be measured by the self-reported Hamilton Depression Rating Scale (HAM-D_6_). Data will be collected at baseline, after 2 weeks, and after 4 weeks. The investigators will measure the change in self-reported symptoms of depression between periods. For each patient, the difference between the scores measured at the first and last visit (2 weeks apart) of the exposure sequence will be subtracted from the difference between the scores measured at the first and last visit (2 weeks apart) of the control period. The total sum scores between 0 and 50 will be reported, where higher values represent worse outcome.Insomnia Severity Status will be measured by questionnaire using the Insomnia Severity Index (ISI). Data will be collected at baseline, after 2 weeks, and after 4 weeks. The investigators will measure the change in patients’ insomnia severity status between periods. For each patient, the difference between the scores measured at the first and last visit (2 weeks apart) of the exposure period will be subtracted from the difference between the scores measured at the first and last visit (2 weeks apart) of the control period. The total scores between 0 and 28 will be reported, where higher values represent worse outcomes.Patients self-reported symptoms of depression measured by questionnaire using the Major Depression Inventory (MDI) [time frame: data will be collected at baseline (visit 2), after 2 weeks (visit 3), and after 4 weeks (visit 4)]. The investigators will measure the change in self-reported symptoms of depression between periods. For each patient, the difference between the scores measured at the first and last visit (2 weeks apart) of the exposure period will be subtracted from the difference between the scores measured at the first and last visit (2 weeks apart) of the control period. The total score between 0 and 50 is reported, where higher values represent worse outcomes.Symptoms of anxiety will be measured by questionnaire using the Beck Anxiety Index (BAI). Data will be collected at baseline (visit 2), after 2 weeks (visit 3), and after 4 weeks (visit 4).The investigators will measure the change in self-reported symptoms of anxiety between periods. For each patient, the difference between the scores measured at the first and last visit (2 weeks apart) of the exposure period will be subtracted from the difference between the scores measured at the first and last visit (2 weeks apart) of the control period. The total score between 0 and 63 for each visit is reported, where higher values represent worse outcomes.Patient-reported outcomes concerning interpersonal sensitivity, neurasthenia, anxiety, and depression will be measured by questionnaire using The Self-Reported Symptom State Scale (SCL-28) [time frame: data will be collected at baseline (visit 2), after 2 weeks (visit 3), and after 4 weeks (visit 4)]. The investigators will measure the change in self-reported symptoms between period A and B or B and A. For each patient, the difference between the scores measured at the first and last visit (2 weeks apart) of the exposure period will be subtracted from the difference between the scores measured at the first and last visit (2 weeks apart) of the control period. Sub scales are combined to compute a total score. The range for each sub scale is: Interpersonal Sensitivity 0–32, Neurasthenia 0–28, Anxiety 0–32, and Depression 0–24. Both total score and sub scale scores will be reported. The total score ranges between 0 and 112, where higher value represents worse outcomes. Because of an overlap in one question between the sub scales anxiety and depression question, number 31 is only considered in the total sum scores.

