### Data collection methods

The following data will be collected for the purpose of the research and recruitment:
From hospital records: Name, phone number, personal identification number from the Danish Civil Registration System (CPR number), diagnosis, medication prescriptions.From actigraphy (Motionlogger Micro Watch from Ambulatory Monitoring Inc. NY): Total sleep time, sleep onset latency, number of awakenings, wake after sleep onset.From diaries: The use of sleep and anxiety medications, bedtime and time of getting out of bed, number of awakenings and duration, wake after sleep onset and daytime naps including lengths registered in minutes.From six validated questionnaires: The Global PSQI Score using The Pittsburgh Sleep Quality Index (PSQI), the insomnia severity score using the Insomnia Severity Index (ISI), depressive symptoms using the Major Depression Inventory (MDI) and 6-item Hamilton Rating Scale for Depression (HAM-D_6_), patients’ self-reported symptoms using the Self-reported Symptom State Scales (SCL-28) and anxiety symptoms using the Beck Anxiety Index (BAI) [3, 25, 28–30].

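### The SCL-28 rule for item 31 contradicts the stated Anxiety and Depression subscale ranges; as a minor correction, the HAM-D6 range of 0–50 does not fit a six-item scale

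*Protocol article*

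**What the plan says.** All but one of the statements are in the Protocol article, Secondary outcome measures.

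**SCL-28.** The total is formed from the subscales: "Sub scales are combined to compute a total score". The subscale ranges are "Interpersonal Sensitivity 0–32, Neurasthenia 0–28, Anxiety 0–32, and Depression 0–24". For the total: "The total score ranges between 0 and 112, where higher value represents worse outcomes". The total and the four subscales are both to be reported. The item rule opens with its reason, "Because of an overlap in one question between the sub scales anxiety and depression question", and concludes that "number 31 is only considered in the total sum scores".

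**HAM-D6.** The outcome entry says: "The total sum scores between 0 and 50 will be reported, where higher values represent worse outcome". Data collection methods names the instrument as the "6-item Hamilton Rating Scale for Depression", and the Abbreviations list also calls it a 6-item scale. The MDI entry, two entries further on, says: "The total score between 0 and 50 is reported, where higher values represent worse outcomes".

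**The concern.** The item-31 sentence is a scoring instruction. As worded, it confines the item to the total, so the item would not contribute to either subscale that shares it. The subscale ranges printed just before it only make sense if the item does contribute. An analyst who codes from the sentence and one who codes from the ranges would therefore compute different Anxiety and Depression scores from the same answers.

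That reaches the results. Each subscale is reported and analysed as a change over the blanket period set against a change over the control period. If item 31 is dropped, its contribution is dropped from those differences too. The safeguard described under The practicalities of the trial, making every question a required field, catches missing answers but not a wrongly built subscale.

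The HAM-D6 range is a different kind of slip. It is a printed maximum that does not suit the number of items and is the same as that of another depression scale. What is at stake there is the accuracy of the outcome definition and how a reader interprets the size of a change.

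**Working it through.** **Inputs** (Protocol article, Secondary outcome measures, unless noted)
- SCL-28 subscale maxima: Interpersonal Sensitivity 32, Neurasthenia 28, Anxiety 32, Depression 24.
- SCL-28 total maximum: 112.
- Overlap: one question shared by Anxiety and Depression.
- HAM-D6: six items (Data collection methods), stated maximum 50. MDI: stated maximum 50.
- Points per item: not stated for either scale.

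**Step 1. Points per SCL-28 item (inferred).** If the 28 in the name is the number of items, 112 / 28 = 4. The overlap gives the same value. The subscale maxima sum to 32 + 28 + 32 + 24 = 116, and 116 − 112 = 4, which is one item's maximum. Equal item maxima of 1 or 2 also divide every stated range, but they imply 112 or 56 distinct items and an overlap of 4 or 2 items. Only 4 gives 28 items and one overlap. At 4 points the subscales hold 8 + 7 + 8 + 6 = 29 places, and one shared item leaves 28.

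**Step 2. Reproduce the stated total.** 116 − 4 = 112 = 28 × 4. The stated 0–112 is reproduced exactly, with the shared item counted once.

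**Step 3. Apply each reading of the item-31 rule.**

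| Reading | Anxiety max | Depression max | Total max | Agrees with stated 32 / 24 / 112? |
|---|---|---|---|---|
| Item 31 in both subscales, once in the total | 32 | 24 | 116 − 4 = 112 | Yes, all three |
| Literal: item 31 in the total only, taken out of both subscales | 32 − 4 = 28 | 24 − 4 = 20 | 32 + 28 + 28 + 20 + 4 = 112 | Total yes, both subscales no |
| Literal, with the stated subscale ranges taken as already excluding item 31 | 32 | 24 | 116 + 4 = 120 | Subscales yes, total no |

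Neither literal reading fits all the stated ranges. The first reading does, but the sentence does not say it.

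**Step 4. Size.** Under the literal reading that keeps the total at 112, the loss is 4/32 = 12.5% of the Anxiety range and 4/24 = 16.7% of the Depression range. The total is the same for every patient under the first two readings, because both count the 28 distinct items once each.

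**Step 5. HAM-D6.** 50 / 6 = 8.33. With equal whole-number scoring the maximum must be a multiple of 6. The nearest are 48 (8 points per item) and 54 (9 points per item), so 50 cannot occur. The actual maximum cannot be derived, because item scoring is not given. If items ran to 2, 3 or 4 points (an assumption), it would be 12, 18 or 24.

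**The case against.** The strongest reply is that the SCL-28 text explains itself. It names the overlap, and the stated total is exactly what one shared item counted once produces. A careful reader will conclude that item 31 should be counted only once in the total. On this view the sentence is merely awkward, and the percentage losses arise only if someone follows it against the printed ranges. The point about intent is persuasive, and it is why the total should be left alone. It does not rescue the sentence, which places the item in the total only, whereas the ranges require it in two subscales as well. A scoring rule should not have to be corrected by inference from the ranges beside it.

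Several stronger readings are tempting and should not be drawn:
- **That the SCL-28 total is wrong because the subscales add to 116.** This treats combining as plain addition and ignores the overlap sentence, which accounts for the 4 points.
- **That the literal rule leaves a total of 108.** The sum 32 + 28 + 28 + 20 = 108 omits item 31, which the rule itself puts back: 108 + 4 = 112.
- **That the HAM-D6 maximum is overstated by at least a factor of two.** This depends on assumed item maxima of up to 4. Even the bar on 50 assumes equal whole-number scoring. Copying from the MDI entry is a plausible explanation, but it is not documented.
- **That data capture is set up with wrong limits.** The article mentions required fields in REDCap and no range limits.

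It is also fair to say that a misprinted HAM-D6 maximum enters no score, difference or test. That stands in full.

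Fuller scoring instructions may exist in a document not shown. The point does not rest on their absence, only on two statements in the article that cannot both be followed.

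**Conclusion.** The point holds for the SCL-28 item rule. As written, it conflicts with the stated ranges of two reported subscales. Followed literally, it would reduce Anxiety to 0–28 and Depression to 0–20, a loss of 12.5% and 16.7% of their ranges. The stated total of 0–112 is correct and does not depend on which of the two main readings is used. The figures assume 0–4 per item, which is inferred from 112/28 and from the 4-point gap, not stated.

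The HAM-D6 range of 0–50 is a minor, near-clerical error. It matches the MDI range and does not fit six items with equal whole-number scoring. The correct maximum cannot be given from the documents.

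Both matters concern secondary outcomes only. Total sleep time, its test and the sample size based on it are untouched, as are the HAM-D6 within-patient differences, which do not use the printed range. This is a low-severity correction, worth making because the SCL-28 rule could change reported subscale results.

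**What to change.** 1. Replace the item-31 sentence with: *item 31 is scored in both the Anxiety and the Depression subscale and counted once in the total (maximum 112).* Check the scoring syntax against it: the subscale maxima should come out at 32, 28, 32 and 24 and the total maximum at 112.
2. Replace the HAM-D6 range with the one on the scoring sheet of the self-report version in use.

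The cost is two sentences of wording and a short check of the scoring code. No design feature, visit or primary analysis changes.

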
### Sample size

The power calculation is based on data from a pilot study (*N* = 8) as we have not identified any studies investigating the effects of ball blankets on TST in depressed patients.

The main outcome will be changes in total night-time sleep with and without PBB estimated by the means of the differences between the periods for each participant. The null hypothesis is that there is no change in sleep duration. In the pilot study, the mean sleep duration appeared normally distributed and the mean sleep duration without a ball blanket was 420 min. The standard deviation of the difference between the sleep duration with and without a ball blanket was 42 min. Based on the potential clinical gains, we aim to be able to detect a change in total sleep duration of 20 min. Assuming that the differences in sleep duration with and without a ball blanket is normally distributed, we performed power calculations for a paired *t* test, and with an alfa = 0.05 and power = 0.80 the minimum required sample size is *N* = 37. To take into account dropout rates, we aim to include 45 patients.

### Recruitment

Patients will be recruited through dedicated teams of nurses, doctors, and psychologists at each hospital. [name] or research assistants will participate in weekly treatment conferences in order to help the nurses identify participants according to the eligibility criteria. When potential participants are identified, the primary contact nurse will perform the first contact. She will briefly inform them about the project and hand out the leaflet “Ball blankets as a treatment option for sleep disturbances”. In cases where patients show interest, the primary contact nurse will ask for oral permission for [name] or one of the research assistants to make contact with them by phone. The contact nurse will also ask for permission to pass on the following information to [name] or the research assistants from their medical journal before signing the written consent for participation: their phone number, ICD-10 diagnosis, actual medication prescriptions, and symptoms of sleep disturbances. Shortly after, [name] or the research assistants will contact the patient and go over the inclusion criteria on the phone in order to verify the patients’ ability to participate. Further, patients will receive oral information on the aim, methods, benefits, and consequences of participation by phone and will be asked for permission to receive written patient participation material by e-mail. This enables the patients to read the material in quiet surroundings in cooperation with a relative. The material is concisely and precisely formulated in order to be easily understood by patients with potential cognitive deficits. Three to 5 days later, [name] or one of the research assistants will make contact with the patients in order to confirm or disconfirm their interest in arranging a meeting. At a meeting, oral information on the project will be repeated and questions will be answered for the purpose of gaining written consent. Before signing the consent, each patient will be given a 1-week period for deliberation. The consent will give [name] or the research assistants the right to gather the relevant information necessary for the analyses, i.e. medication use and diagnosis. The information will be given by [name] or the research assistants in a quiet and undisturbed meeting room at the hospital in the presence of a relative. No further information from patients’ medical journal will be gathered after the signing of the written consent unless patients inform us of changes in diagnosis or medication prescriptions. The written consent will be uploaded and stored in REDCap.

If the inclusion rate is unexpectedly low, additional outpatient clinics from other university hospitals will be included.

### Allocation

The randomization procedure is permuted-block randomization with varying block sizes of 4, 6, and 8 generated by an independent service provider using REDCap for randomization, meaning detailed information on blocking is unavailable to those who enrol participants and assign interventions. [name] and the research assistants have access to the randomization module in REDCap as data will be entered and stored in REDCap. [name] and the research assistants will be informed of allocation sequences by pressing the randomization button in REDCap. The allocation sequence is not concealed from the outcome assessors ([name] and the research assistants).

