### Eligibility criteria

Patients will be recruited through their primary contact in the clinics. The project manager (PhD student and psychiatric nurse ([name])) and three research assistants (two psychiatric nurses and a medical student) will perform the interventions.

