#### Actigraphy

Actigraphy will be used as an instrument to objectively evaluate sleep in this trial.

The devise used is a Motionlogger Micro Watch (Version 1.99.5.1.) from Ambulatory Monitoring Inc. New York, USA. It is a portable device that is the size of a large wristwatch. The actigraph is an accelerometer that detects the intensity and the amount of movements as a function of time [26]. Movements are monitored continuously and stored within the device. Subsequent analysis of frequency and patterns of movement by means of validated algorithms permits detection of sleep-wake patterns. For this trial, movements will be sampled in 1-min epochs. The data activity collection modes are Zero Crossing (ZC) and Proportional Integrating Measure (PIM) [26, 27]. All movements that are scored above a preset threshold using the algorithm Cole-Kripke scoring algorithm are scored as “awake” and those that are below this threshold are scored as “sleep”. The algorithm correctly distinguished sleep from wakefulness 88% of the time when compared to polysomnography [27].

All patients will be asked to wear the actigraph on the wrist of their non-dominant hand for the consecutive 4 weeks (28 nights in total) in their own home environments. As the device is waterproof, patients are instructed to wear the actigraph 24 h a day, including when taking showers. Patients are instructed to press the event-marker as they go to bed, wake up, and when they get out of bed at the start of the next day. These starts and stop intervals will be registered in sleep diaries as patients will be able to visually see if they forgot the registration.

[name] and an experienced sleep scientist will perform the scoring and analysis of actigraphic records. The degree of agreement between raters will be calculated and reported using the Intraclass Correlation Coefficient. Data will be analysed using the MotionLogger Analysis Software program Action-W (AW2) (Version 2.7.2).

The pertinent sleep variables chosen for this trial are total sleep time after sleep onset (in minutes) (TST), sleep onset latency (SOL), number of awakenings, and wake after sleep onset (WASO) (for definitions of variables, see the “Outcomes” section).

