**Fig. 2 Fig2:**
[figure not shown]
Study schedule for enrolment, intervention, and assessments

The participant timeline (Fig. 1) shows patients will meet with data collectors four times in total. Initially for the purpose of recruitment and written consent (visit 1), the second visit (Visit 2) consists of the installation and activation of actigraphs. Baseline data will be gathered using six validated questionnaires (see the “Data collection methods” section for further details). Patients will be introduced to the sleep and medication diary (Table 2) presented as a supplementary material. Data from sleep diaries will be used to aid the process of scoring sleep-wake stages, when analyzing patients’ actigraphic sleep records. Subsequently, patients are randomized into either (1) sequence “AB” or (2) sequence “BA” each lasting 4 weeks. Patients randomized to the AB sequence receive treatment A (Protac Ball Blanket™, Flexible, 7 kg) in the first 2 weeks (14 nights) and switch to treatment B (treatment as usual = regular duvet) in the second period, whereas patients that are randomized to the BA sequence receive treatment B in the first period and treatment A in the second period. This means that participants will serve as their own controls.

In both sequences, patients receive general sleep advice prior to participation [4]. The rationale behind this is to avoid behavioural irregularities between periods in order to make comparison of data possible. Patients are recommended to avoid major variations in their sleep-wake patterns from day to day during the trial. But also to avoid major variations in their sleep environment and nicotine, caffeine, alcohol and food consumption directly before bed. Patients are also advised to limit daytime naps to a maximum of 30 min.

The third visit (visit 3) at day 15 consists of a switch-over visit to either receive the intervention or treatment as usual. All six questionnaires will be repeated. Data concerning sleep and medication will be downloaded from actigraphy and collected from diaries for the first 2-week period (14 days and nights). The procedures will be repeated at the end of the study (week four = day 29) at visit 4.

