### Blinding

The administration of blankets will be performed in a randomized order but blinding of the patients and operators is not possible. The data analyses will be performed blinded to the sequence (“AB” or “BA”, described above).

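### At least one of the two scorers of the actigraphy behind the primary outcome appears to know the allocation, and the stated blinding of the analyses does not clearly cover scoring

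*Protocol article*

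**What the plan says.** All references are to the protocol article.

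- **Who scores.** Under Actigraphy, two people handle the records: one whose name is removed, and a second, so that the sentence ends "an experienced sleep scientist will perform the scoring and analysis of actigraphic records". Agreement between them is to be reported: "The degree of agreement between raters will be calculated and reported using the Intraclass Correlation Coefficient".
- **Who knows the sequence.** Under Allocation, a person whose name is removed and the research assistants obtain it themselves: "the research assistants will be informed of allocation sequences by pressing the randomization button in REDCap". The section adds: "The allocation sequence is not concealed from the outcome assessors", and lists those assessors as the same person and the research assistants. The sleep scientist is not listed.
- **Who delivers the treatment.** Under Eligibility criteria, the project manager (name removed) works with the assistants: "three research assistants (two psychiatric nurses and a medical student) will perform the interventions".
- **How scoring is done.** The Cole-Kripke algorithm classifies 1-min epochs against a preset threshold (Actigraphy). The night runs from 21:00 to 08:59, with a rule for the first sleep episode (Primary outcome measure). The text on trial practicalities adds: "Data from sleep diaries will be used to aid the process of scoring sleep-wake stages".
- **What is blinded.** Under Blinding, "blinding of the patients and operators is not possible", but "The data analyses will be performed blinded to the sequence".

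**The concern.** The patient knows which blanket is in use, and the other listed outcomes, apart from the actigraphic ones, are questionnaires or diary entries by that patient. Actigraphic TST is therefore the endpoint best placed to resist expectation, provided its scoring does not bring expectation back in.

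A scorer who knows the sequence and sees the date knows the treatment on each night. If judgement calls on where a sleep interval starts or ends lean towards one treatment, the error attaches to treatment rather than to period. Randomising the order then does not cancel it, and a later analysis blinded to sequence cannot remove it. Ordinary scoring error that is unrelated to treatment would only add noise.

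**Working it through.** **1. Is a scorer unblinded?** The removed name appears as a scorer (Actigraphy), as a person who obtains the sequence and as an outcome assessor (Allocation), and as the project manager who delivers the intervention (Eligibility criteria). I assume these are one role. On that assumption one of the two scorers is documented as knowing the sequence. Nothing is said about what the sleep scientist knows.

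**2. Does knowing the sequence reveal the treatment?** Each sequence is 14 nights of one treatment followed by 14 of the other. First-period data are downloaded at visit 3 and second-period data at visit 4, so sequence plus date identifies the treatment. Under Data management, sleep data carry no personal identifiers but are stored under the REDCap ID. REDCap is also where these staff obtain the allocation, so that ID does not mask it from them.

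**3. Does scoring leave room for judgement?** Partly. The epoch threshold and the night window are fixed. The interval, however, is set with the help of diaries and of event markers that patients may forget to press, and an agreement statistic between raters would have little purpose if scoring were wholly mechanical.

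**4. Does the stated blinding cover scoring?** Actigraphy speaks of scoring and analysis of records by the same two people. Blinding speaks of data analyses. Allocation says the assessors know the sequence. If Blinding refers only to the statistical step, all three statements can stand together and TST scoring is unmasked. If it was meant to include scoring, it conflicts with Allocation as far as the project staff member is concerned.

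**5. What would a given shift do?**

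Inputs from Sample size and Statistical methods: target difference 20 min, SD of the within-patient difference 42 min, two-sided alpha 0.05, power 0.80, paired t test, N = 37, planned inclusion 45.

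Rejection probability for a mean difference b with n pairs: P(T > t) + P(T < −t), where t is the 97.5% point of the t distribution on n − 1 degrees of freedom, and T is noncentral t with λ = b√n / 42.

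The protocol's own figure first: b = 20, n = 37 gives λ = 20 × 6.083 / 42 = 2.90 and power 0.805. This is the smallest n that reaches 0.80, so N = 37 reproduces. The blinding point does not affect it.

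Now set the true effect to zero and let b be a scoring shift. **The values of b are assumptions; the document gives none.** The SD is kept at 42.

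| Assumed mean shift | λ, n = 37 | Two-sided rejection, n = 37 | λ, n = 45 | Two-sided rejection, n = 45 |
|---|---|---|---|---|
| 0 min | 0 | 5.0% | 0 | 5.0% |
| 2 min | 0.29 | 5.9% | 0.32 | 6.1% |
| 5 min | 0.72 | 10.9% | 0.80 | 12.2% |
| 10 min | 1.45 | 29.2% | 1.60 | 34.6% |

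If the shift favours the blanket, nearly all of the excess is false claims of benefit: at n = 37 the probability of a significant result for the blanket goes from 2.5% to 4.7%, 10.5% and 29.1%.

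**The case against.** The other side has several good points.

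- **Two scorers, one documented as unblinded.** A reader might infer that both know the allocation. The documents do not support that: the sleep scientist is absent from the list of unblinded assessors. Even for the first scorer, the link rests on a removed name.
- **Other safeguards exist.** A reader might infer that masked scoring was the only protection and has been abandoned. In fact there is a preset threshold, patient-pressed event markers, a fixed night window with a first-episode rule, and a second rater. These narrow the discretion but do not remove it.
- **The agreement statistic has some value.** If the sleep scientist is unaware of allocation, comparing the two raters could expose a lean in the other one. But the intraclass correlation as planned is an overall agreement measure. It is not a check for a treatment-related difference, and it would miss a lean that both raters shared.
- **No strict contradiction.** Unblinded assessment and a blinded statistical analysis can coexist. The list of assessors might also refer mainly to visits and questionnaires. The article does not settle this, which is a reason to reconcile the sections.
- **A 20 min artefact is not shown.** A reader might infer that moving each end of the interval by 10 min (10 + 10 = 20) would manufacture the whole target effect, 20/420 = 4.8% of the pilot mean. That is a theoretical ceiling. TST excludes sleep latency and wake after sleep onset, so added minutes count only if the algorithm calls them sleep, and the edges of the night are where wake is most likely. The shift would also have to average 20 min over all blanket nights and all patients.
- **The article condenses a fuller protocol.** True, but the point rests on an explicit statement that assessors are not masked, not on a missing detail.

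**Conclusion.** The concern holds in this limited form. At least one of the two scorers of the primary-outcome records appears to know the allocation, scoring keeps some judgement, and the stated blinding does not clearly reach it. This is a stated feature of the design that can bias TST, and it should be changed or clarified.

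The size and direction of any bias are unknown. The figures of about 6%, 11% and 29% show sensitivity under assumed shifts of 2, 5 and 10 min at n = 37; they are not estimates. They rest on the pilot SD of 42 min (N = 8), normal differences, and a shift that moves the mean without changing the SD. The conclusion about who is unblinded rests on the removed name being the project manager throughout.

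**What to change.** Reconcile Actigraphy, Allocation and Blinding by stating who scores, from what files, and what they know. Specifically:

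1. Give each patient's two 14-night records separate random codes, and remove calendar dates and period order. Keep clock time, which the night window needs.
2. Supply scorers with diary bed and rise times only.
3. Have the recoding done by someone who does not score, for example a research assistant or the independent REDCap provider. The article describes no separate data-management staff, so this role has to be assigned.
4. Use the sleep scientist's scores for the primary TST analysis, provided that person scores all records and is kept unaware of allocation. Use the project staff member's scores for the intraclass correlation only.
5. Lock the scores before the codes are linked to sequence.

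The cost is a small amount of file handling per record. No new reader is needed, but the sleep scientist must score every record; the article does not say whether all or a subset was intended. Sample size, visits and patient burden are unchanged. Recruitment was planned to run until May 2021, after the article appeared, and records already downloaded could be rescored from the stored files.
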